## Abstract

**Background:**

Persons involved in the justice system are at high risk for HIV and drug overdose upon release to the community. This manuscript describes a randomized controlled trial of two evidence-based linkage interventions for provision of HIV prevention and treatment and substance use disorder (SUD) services in four high risk communities to assess which is more effective at addressing these needs upon reentry to the community from the justice system.

**Methods:**

This is a 5-year hybrid type 1 effectiveness-implementation randomized controlled trial that compares two models (Patient Navigation [PN] or Mobile Health Unit [MHU] service delivery) of linking justice-involved individuals to the continuum of community-based HIV and SUD prevention and treatment service cascades of care. A total of 864 justice-involved individuals in four US communities with pre-arrest histories of opioid and/or stimulant use who are living with or at-risk of HIV will be randomized to receive either: (a) PN*,* wherein patient navigators will link study participants to community-based service providers; or (b) services delivered via an MHU*,* wherein study participants will be provided integrated HIV prevention/ treatment services and SUD services. The six-month post-release intervention will focus on access to pre-exposure prophylaxis (PrEP) for those without HIV and antiretroviral treatment (ART) for people living with HIV (PLH). Secondary outcomes will examine the continuum of PrEP and HIV care, including: HIV viral load, PrEP/ ART adherence; HIV risk behaviors; HCV testing and linkage to treatment; and sexually transmitted infection incidence and treatment. Additionally, opioid and other substance use disorder diagnoses, prescription, receipt, and retention on medication for opioid use disorder; opioid and stimulant use; and overdose will also be assessed. Primary implementation outcomes include feasibility, acceptability, sustainability, and costs required to implement and sustain the approaches as well as to scale-up in additional communities.

**Discussion:**

Results from this project will help inform future methods of delivery of prevention, testing, and treatment of HIV, HCV, substance use disorders (particularly for opioids and stimulants), and sexually transmitted infections for justice-involved individuals in the community.

*Trial registration:* Clincialtrials.gov NCT05286879 March 18, 2022.

## Background

Stimulant and opioid use are causing an increasing number of overdose deaths and are also fueling new HIV epidemics in the United States (US) [1–3]. Justice-involved individuals represent an underserved and vulnerable population with higher prevalence of substance use disorders (SUDs), [4] HIV and hepatitis C virus (HCV) than those in the general population [5–7]. A substantial proportion of people living with HIV (PLH) in custody are not engaged in HIV care prior to incarceration and, even when provided care during custody, subsequent engagement and retention in HIV care and viral suppression (VS) drop dramatically after release [8]. For individuals involved in the justice system, there is a unique opportunity to provide access to medications for opioid use disorder (MOUD) [9] and other substance use disorder treatments, as well as to engage them in the full cascade of evidence-based HIV prevention (PrEP) and treatment (antiretroviral therapy, ART) services. Therefore, expedited linkage to integrated services has the potential to substantially reduce the risks of justice-involved individuals acquiring and transmitting HIV and HCV infections while in the community.

The US Department of Health and Human Services developed the *Ending the HIV Epidemic in the US* plan [10, 11] which highlights the need for diagnosing, treating, preventing, and predicting HIV infections. Specifically, this plan includes the prevention strategy of providing PrEP for those at risk for acquiring HIV. However, people involved in the justice system without HIV do not typically access PrEP [12–14]. Furthermore, persons who are prescribed PrEP prior to entering the justice system often lose access to their medication upon incarceration. Evaluation of interventions to improve linkage to and receipt of HIV prevention and treatment services as well as SUD treatments are urgently needed for justice-involved populations. Two models of care, Peer/Patient Navigation (PN) and Mobile Health Units (MHUs), have been shown individually to have some success in engaging persons in substance use and HIV related care; however, there have been few evaluations comparing these models with respect to prevention, testing, and treatment of HIV, HCV, and substance use among justice-involved persons [15].

PN models have emerged as effective interventions to improve retention in HIV care and ART adherence upon release to the community for justice-involved persons [16]. In a large, randomized trial of a structured behavioral intervention administered by a peer navigator among PLH being released from the Los Angeles County Jail, VS was maintained in 49.6% of the PN group compared to 36% of controls who received standard transitional case management alone [17]. Similar outcomes have been reported among PLH receiving care in specialized “transitions clinics” where peer navigators assist released PLH with primary care [18]. PN have been found to be effective in supporting linkage to and engagement in MOUD treatment [19]. Despite this evidence and recommendations by the Centers for Disease Control and Prevention [20], PN services are available in few jurisdictions and community clinics around the US and have not been evaluated for the full HIV, HCV, and SUD care cascades for persons receiving these services.

MHUs have demonstrated the potential to serve as a cost-effective clinical model to deliver healthcare services to underserved populations [21–23]. By being able to be flexibly located and embedded within underserved communities, MHUs’ outreach capabilities include an expanded reach to individuals not typically served by traditional health care systems and can overcome structural barriers to care such as transportation and health system complexity [22, 24]. By offering healthcare in a way that is more patient-centric (i.e., convenient locations, familiar environment, informal setting, and culturally competent staff) [22, 25], MHUs tend to build more trust in relationships with the communities they serve. Study results support the favorable impact MHUs have on improved individual health outcomes as well as population health; they also have the potential to reduce healthcare costs when compared to traditional clinical settings [22]. MHUs can also address both social determinants of health by reaching into underserved communities to overcome structural barriers to care. However, MHUs have not been evaluated with respect to the specific delivery of combined HIV, HCV, and SUD care cascades for justice-involved persons. Therefore, rigorous evaluation of the two models of service delivery for the full range of HIV, SUD (particularly OUD), and HCV care cascades is needed for justice-involved persons. This study will compare PN and MHU provision of care to improve linkage to and engagement in HIV, HCV, and SUD prevention and treatment services in four distinct geographic communities in the US.

## Methods

### Study design and settings

ACTION (Addressing risk through Community Treatment for Infectious disease and Opioid use disorder Now) is a five-year hybrid type 1 effectiveness-implementation randomized control trial which compares noninferiority of two models of linking justice-involved individuals to the continuum of community-based HIV and SUD prevention and treatment service cascades of care funded by the National Institute on Drug Abuse. Adults with a history of opioid and/or stimulant use who are currently incarcerated or were involved with the justice system within the past 30 days will be recruited across two Connecticut communities (New London and Windham/Tolland/Middlesex Counties) and two Texas communities (Dallas and Tarrant Counties). A total of 864 participants will be enrolled in the project, 216 from each of the four project sites. Participants will be randomized 1:1 to one of two models of care: (1) a PN for linkage to care, or (2) services delivered via a MHU for a six-month intervention period in each model. For the PN arm of the study, the navigators will assist in linking study participants to appropriate community service providers. Services include SUD treatment, including MOUD, and HCV testing and treatment. PLH will receive assistance with gaining initial or continued access to antiretroviral therapy (ART) services, and those at risk for HIV will be provided access to PrEP services. For those randomized to the MHU arm of the study, these clinical services will be provided along with the assistance of a community health worker (CHW) on board the MHU. When possible, participants will receive PrEP/ART services and prescriptions, SUD screening and diagnoses, MOUD prescription, and harm reductions services on the MHU. If a service cannot be provided directly on the MHU, participants will be linked to the appropriate community-based service providers. This study is multi-site collaboration with Yale University, the University of Texas Southwestern, and Texas Christian University, along with their community and justice system partners. The study has been funded from September of 2020 through August of 2025.

### Project aims

The primary aim of this study is to compare the effectiveness of PN versus MHU service delivery on participant length of time to initiation of PrEP or ART medication following release from custody, or post-randomization for those enrolled in the community (Fig. 1). Additional outcomes will examine the continuation of PrEP or HIV care, including (but not limited to) viral suppression, PrEP adherence, and HIV risk behaviors. The secondary aim of this study is to evaluate PN and MHU feasibility and acceptability. Additional aims include assessing cost offsets and effectiveness, as well as the effectiveness of outcomes among a sub-study of people who inject substances. Additional outcomes will examine broader community health care impact, including other health services accessed, expanded SUD services, and common barriers (e.g., stigma) to service access across the community provider spectrum.

**Fig. 1 Fig1:**
[figure not shown]
Project design

### Sample size and power calculations

The primary outcome analysis will compare the effectiveness of using either PN or MHU, with the outcome being the length of time it takes for study participants to take their first dose of recommended medications (ART for PLH or PrEP for those at risk for HIV) post randomization. We hypothesize that the MHU arm will be superior to the PN arm, given the convenience and flexibility of the delivery of services. We expect that around 5% of our sample will be PLH and 95% will be at risk for HIV. We also expect 80% retention at the 6-month follow-up assessment. Using SAS PROC Power [26] for comparing two survival curves with log-rank test, we found that 864 recruited participants are needed (evenly distributed across study sites, n = 216 per project site; to achieve a sample size of 689 at 6-month follow-up) under the assumptions of alpha = 0.05 and 80% power to detect a hazard ratio (HR) between 1.25 and 1.30 for main effects of treatment arms. The effect size is based on the literature on PLH referred to ART and people at risk for HIV referred to PrEP. For PLH, 64% of the patients in the treatment condition (designed to facilitate initiation of ART) compared to around 51% of patients in standard care within 10 months [27], yielding hazard ratio of 1.25 comparing the MHU group to the PN group.

For the those at risk for HIV and at high risk of contracting sexually transmitted infections (STIs), the drop-off between PrEP referral to PrEP initiation may be as high as 90% [27–29]. To our knowledge, there are no published studies of PrEP uptake among justice-involved populations, although several papers describe low knowledge of PrEP and moderate levels of interest in taking PrEP among people who inject drugs and justice-involved persons [30–33]. A recent paper indicated that 25% of incarcerated persons reported being interested in taking PrEP after release [30]; given actual uptake generally is lower than reported intention, we assumed that the uptake would be between 10% in the PN group and 20% at best in the MHU group given easier access.

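### The target hazard ratio, the assumed uptake and the sample size do not fit together: the plan's own rates give about 118–148 initiations, where 80% power for HR 1.25–1.30 needs 457–631

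*Protocol article*

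**What the plan says.** All the figures are in the protocol article, section Sample size and power calculations, unless noted.

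- Method: "Using SAS PROC Power [26] for comparing two survival curves with log-rank test". Whether the test is one- or two-sided is not stated, and no event count or overall event rate is given.
- Size: "we found that 864 recruited participants are needed", in order "to achieve a sample size of 689 at 6-month follow-up", because "We also expect 80% retention at the 6-month follow-up assessment".
- Claim: alpha 0.05 and "80% power to detect a hazard ratio (HR) between 1.25 and 1.30 for main effects of treatment arms".
- Mix: about 5% of the sample living with HIV and 95% at risk.
- Effect for those living with HIV: 64% starting ART in a facilitated condition against about 51% in standard care, "within 10 months [27], yielding hazard ratio of 1.25 comparing the MHU group to the PN group".
- Effect for those at risk: "we assumed that the uptake would be between 10% in the PN group and 20% at best in the MHU group given easier access".

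Allocation is 1:1 (Study design and settings). PrEP initiation is counted within the 6-month intervention period, and the same approach is used for ART (Analytic plan).

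**The concern.** A log-rank test gains its power from events, here first doses of PrEP or ART, and not from the number enrolled. A hazard ratio as small as 1.25–1.30 needs several hundred events. The same section expects only one in ten to one in five of nearly the whole sample to start medication, so that many events cannot arise from 864 people.

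The effect size has a separate fault. Neither pair of percentages corresponds to a hazard ratio of 1.25–1.30.

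What is at stake is the headline design property. Anyone who relies on the stated power would think that the trial can detect a modest difference between the two models, when on the plan's own rates it can reliably detect only a much larger one.

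**Working it through.** **Inputs from the article:** N = 864 recruited, 689 at 6 months; 80% retention; alpha 0.05; power 80%; HR 1.25–1.30; 1:1 allocation; 95%/5% mix; PrEP uptake 10%/20%; ART initiation 51%/64%. **Assumptions:** two-sided test as the base case, one-sided as a check; the 10-month ART rates applied unchanged to 6 months at first.

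**1. The retention step.** 689/0.8 = 861.25, so 862, close to 864; and 864 × 0.8 = 691. This step is sound.

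**2. Events needed** (Schoenfeld, 1:1): d = 4(1.96 + 0.8416)²/(ln HR)².
- HR 1.25: 630.5, so 631. That is 92% of 689 or 73% of 864.
- HR 1.30: 456.1, so 457. That is 66% of 689 or 53% of 864.

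**3. Events expected.** The mean PrEP uptake over the arms is 15% and the mean ART initiation 57.5%. The overall rate is 0.95 × 0.15 + 0.05 × 0.575 = 0.17125.
- 689 × 0.17125 = 118.0
- 864 × 0.17125 = 148.0

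**4. Power with those events:** Φ(½√d · ln HR − z), with z = 1.96 two-sided or 1.645 one-sided.

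| Events | HR 1.25, two-sided | HR 1.30, two-sided | HR 1.25, one-sided | HR 1.30, one-sided |
|---|---|---|---|---|
| 118 | 22.7% | 29.6% | 33.3% | 41.3% |
| 148 | 27.3% | 35.8% | 38.7% | 48.0% |

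The HR detectable with 80% power (two-sided), exp(2 × 2.8016/√d), is 1.68 with 118 events and 1.59 with 148.

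**5. A scenario consistent with HR 1.25–1.30.** The 118–148 events presuppose 20% uptake in the MHU arm. If the PN arm has 10% PrEP and 51% ART and the HR really is 1.25–1.30, MHU PrEP uptake is 1 − 0.9^HR = 12.3–12.8%, and ART is 59.0–60.4%. Events are then 92–94 (N = 689) or 115–118 (N = 864), and two-sided power is 19–25% or 22–30%.

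**6. The hazard ratios implied by the stated percentages:** ln(1 − p₂)/ln(1 − p₁).
- 51% to 64%: ln 0.36/ln 0.49 = 1.43. The stated 1.25 is 64/51 = 1.255, a risk ratio.
- 10% to 20%: ln 0.80/ln 0.90 = 2.12 in PrEP candidates.
- Mixed sample: PN 0.95 × 0.10 + 0.05 × 0.51 = 12.05%; MHU 0.95 × 0.20 + 0.05 × 0.64 = 22.2%; HR = ln 0.778/ln 0.8795 = 1.96. Power is 95% (118 events) to 98% (148).
- If MHU PrEP uptake is 15%: MHU 0.95 × 0.15 + 0.05 × 0.64 = 17.45%; mixed HR 1.49; 102–127 events; power 52–62%.

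**7. Can the stated N be reproduced?** Not from the stated mix. At 17.125% initiating, HR 1.30 needs 457/0.17125 = 2,669 people two-sided, or 2,102 one-sided (360 events), before dropout. Freedman's formula does not help; it needs slightly more events (462 two-sided at HR 1.30). The stated size is approximately recovered only if the ART rates are applied to everyone: 864 × 0.575 = 497 events, for which the detectable HR is 1.29 two-sided, inside the stated range.

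**8. Sensitivity to the 10-month rates.** Scaled to 6 months under a constant hazard, 51%/64% become 1 − 0.49^0.6 = 35% and 1 − 0.36^0.6 = 46%. Events become 112–141 and two-sided power at HR 1.25–1.30 becomes 22–34%.

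**The case against.** The strongest reply is that the trial is well powered for what it assumes. The 118–148 events arise only if uptake is 10% versus 20%, and that contrast has about 95–98% power. This stands. A reader might infer from the low figures that the trial as a whole is underpowered, or that 864 is too few; the article does not support that. The low power applies if the true HR is 1.25–1.30, which is the effect named in the power claim. The article also presents 20% as the most that could be hoped for, so the favourable figure belongs to its best case.

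Sidedness is not stated, so the two-sided range is conditional. A one-sided test raises power to 33–48%, still far from 80%.

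A reader might also infer that a null result is bound to be misread as excluding modest effects. The Analytic plan commits to the hazard ratio with its 95% confidence interval, which would show the imprecision. The fault is in the stated design property, not in the planned reporting.

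It is also tempting to object that the ART figures compare a facilitated programme with standard care, whereas the PN arm here is itself an active intervention. That is a judgement about how far a cited study carries over, not an error that the document shows. The 10-month time frame is a real mismatch, but it concerns 5% of the sample and changes little.

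**Conclusion.** The point holds as an inconsistency among target effect, uptake and sample size. With the article's own mix and rates, 80% power for HR 1.25–1.30 is not delivered: about 118–148 initiations are expected against 457–631 needed, and power is about 23–36% two-sided, or 19–30% when MHU uptake is set to match that HR. What 864 recruits do support is 80% power for HR of about 1.6–1.7.

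The derivation of 1.25 is also wrong as written, because it is a risk ratio; the corresponding HR is 1.43.

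The sizes rest on proportional hazards, a two-sided 0.05 test, and the 10-month ART rates used at 6 months; relaxing the last two, as shown, does not change the conclusion. That the 51–64% rates were applied to the whole sample is a likely explanation of the stated N, but the article does not show the calculation, so it remains an inference.

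**What to change.** Keep N = 864 and rewrite the power paragraph in events, with the sidedness of alpha stated. On a two-sided 0.05 test it would say:

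- about 118 (N = 689) to 148 (N = 864) initiations are expected by 6 months under the assumed mix and uptake;
- these give 80% power for HR of about 1.6–1.7;
- power is about 95–98% for 10% versus 20% PrEP uptake (mixed-sample HR about 1.96), and about 52–62% for 10% versus 15% (mixed-sample HR about 1.49).

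Withdraw the claim of 80% power for HR 1.25–1.30. Call the 1.25 a risk ratio, or correct it to HR 1.43, and note that its percentages are at 10 months while the primary window is 6 months.

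The cost is one rewritten paragraph and a less favourable stated detectable effect. No participants are added. By contrast, keeping HR 1.25–1.30 as the target at this event rate would take about 2,669 (457/0.17125) to 3,685 (631/0.17125) people before dropout.

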## Interventions

### Patient navigation (PN) arm

Our PNs will be individuals that ideally have “shared living experiences” (e.g., HIV or history of SUD treatment) with participants and will help them overcome barriers to accessing and engaging in quality care [15]. We will work with our community partners to assure that our PNs are integrated as members of the community health care teams. The PN will work closely with the study participants to access medication for opioid use disorders, behavioral health for stimulant use and other SUDs, HIV and HCV testing, prevention, and treatment, as well as other primary health care. They will also assist with housing, health insurance, transportation, childcare, and other needs during the six-month intervention. Across all four community sites, ACTION PNs will receive active, comprehensive training and guidance on providing appropriate linkage to community services including harm reduction services such as syringe services programs in Connecticut (not available in Texas) and education on safe injection practices of substances to reduce HIV and HCV infection and reinfection.

The community partners collaborating on this project have extensive experience in PN support services, their PN protocols will provide a guiding framework for the ACTION training protocol. PN training will capitalize on existing linkages to an array of services through Federally Qualified Health Centers or similar organizations, including primary care, substance use treatment, behavioral health, case management, and care coordination. In addition, these services include confidential rapid HIV and HCV testing, education about prevention of HIV and HCV care, PrEP, post-exposure prophylaxis for HIV, and MOUD (buprenorphine and extended-release naltrexone). All PNs will be trained to provide motivational interviewing and goal setting as part of their services provided in the project as it has been shown to improve treatment engagement in persons who use substances [63, 64].

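### The design hazard ratio of 1.25 is a facilitated-care versus standard-care risk ratio labelled as MHU versus PN, and the plan's rates for the trial arms do not support it

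*Protocol article*

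**What the plan says.** All references are to the protocol article. The primary aim (Project aims) is to "compare the effectiveness of PN versus MHU service delivery on participant length of time to initiation of PrEP or ART medication". Sample size and power calculations arrives at 864 recruited and 689 at 6 months "under the assumptions of alpha = 0.05 and 80% power to detect a hazard ratio (HR) between 1.25 and 1.30", by a log-rank test in SAS PROC POWER.

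Two sources for the effect follow.

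- **People living with HIV, about 5% of the sample.** 64% started ART in a condition built to facilitate initiation, "compared to around 51% of patients in standard care within 10 months [27], yielding hazard ratio of 1.25 comparing the MHU group to the PN" arm.
- **People at risk, about 95%.** The section notes that "the drop-off between PrEP referral to PrEP initiation may be as high as 90" percent, cites 25% interest in PrEP among incarcerated people, and assumes uptake of 10% in PN and at best 20% in MHU.

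Elsewhere PN is an active intervention. The Abstract presents both arms as evidence-based linkage interventions. Study design and settings has navigators linking participants to providers. The Patient navigation (PN) arm section says "The PN will work closely with the study participants to access medication for opioid use disorders" and other care, and adds motivational interviewing, goal setting and help with insurance and transport. The Background reports that in a trial of a peer navigator "VS was maintained in 49.6% of the PN group compared to 36% of controls who received standard transitional case management alone".

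**The concern.** The 51% was seen under standard care, and the sizing puts PN in that place. A condition designed to make initiation easier describes PN as well as it describes MHU, so the cited contrast says little about the difference between the two. The value 1.25 is also the ratio of two cumulative proportions, not of two hazards, although it enters a log-rank calculation as a hazard ratio.

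Interpretation is at stake. The section says its effect size rests on the literature. If the trial finds no significant difference, a reader relying on that statement could conclude that a literature-based MHU advantage had been tested with 80% power and not found. The cited literature supplies no such advantage over PN.

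**Working it through.** **Inputs** (Sample size and power calculations, unless noted): alpha 0.05, power 80%, HR 1.25 to 1.30; 864 recruited, 689 retained; 5% living with HIV, 95% at risk; ART 64% versus 51% at 10 months; PrEP 20% versus 10%; 1:1 allocation (Study design and settings); initiation counted within 6 months (Analytic plan). Sidedness is not stated, so two-sided is assumed unless noted.

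**1. The plan's own figures.** The retention step reproduces: 689/0.80 = 861.25, so 862, or 4 × 216 = 864 with equal sites. Events for 80% power, by d = 4(1.96 + 0.8416)²/(ln HR)²:

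- HR 1.25: 631 events, 92% of 689
- HR 1.30: 457 events, 66% of 689

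The stated HR range is approached only if the ART rates are applied to everyone. The mean event proportion is then (0.51 + 0.64)/2 = 0.575.

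- 689 × 0.575 = 396 events: smallest detectable HR 1.325 two-sided, 1.284 one-sided
- 864 × 0.575 = 497 events, with no loss: 1.286 two-sided

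The PROC POWER curves and accrual inputs are not shown, so other inputs may have been used.

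**2. What 64% versus 51% is.**

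- Risk ratio: 0.64/0.51 = 1.25
- Hazard ratio under proportional hazards: ln(1 − 0.64)/ln(1 − 0.51) = ln 0.36/ln 0.49 = 1.43

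**3. What the PrEP assumption implies.** HR = ln 0.80/ln 0.90 = 2.12. No figures in the article yield an HR of 1.25 for MHU versus PN.

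**4. Events from the plan's own rates.** 689 × [0.95 × (0.10 + 0.20)/2 + 0.05 × (0.51 + 0.64)/2] = 689 × 0.17125 = 118. This carries the 10-month ART rates over unchanged. Under a constant hazard the 6-month rates would be 1 − 0.49^0.6 = 35% and 1 − 0.36^0.6 = 46%, and the total about 112.

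Power = Φ(√d/2 × ln HR − 1.96) with d = 118:

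- HR 1.25: 23% (one-sided 33%)
- HR 1.30: 30% (one-sided 41%)

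With all 864 followed, 148 events give 27% and 36%, two-sided.

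**5. Sensitivity to PN uptake in the PrEP stratum.** MHU is held at 20%, with 689 × 0.95/2 = 327.3 per arm, events = 327.3 × (p + 0.20) and HR = ln 0.80/ln(1 − p).

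| PN uptake p | HR | Events | Power |
|---|---|---|---|
| 10% | 2.12 | 98 | 96% |
| 12% | 1.75 | 105 | 81% |
| 13.8% | 1.50 | 111 | 57% |
| 15% | 1.37 | 115 | 40% |

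The 13.8% is 10% × 49.6/36. It borrows a viral suppression ratio and is an illustration only.

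**The case against.** The power statement is conditional. It claims 80% power to detect "a hazard ratio (HR) between 1.25 and 1.30 for main effects of treatment arms", and a poorly sourced HR does not make that conditional claim an arithmetic error. This stands.

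The mislabelled source covers about 43 of 864 participants (5%). For the rest the plan gives its own arm-specific rates, under which power is about 96% in the PrEP stratum. This also stands, but those rates imply an HR of 2.12, so they cannot be the origin of 1.25.

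The design range may already allow for an active PN arm. With MHU at 20%, HR 1.25 to 1.30 corresponds to PN uptake of 1 − 0.80^(1/HR), about 16%, well above 10%. That is fair as to the size of the HR. At those rates, however, the PrEP stratum yields only about 117 to 119 events, and power is again about 23% to 29%.

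Two stronger readings are tempting and are not supported.

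- A reader might divide 1.25 to 1.30 by an assumed PN effect over standard care and report a large loss of power. That starts from a figure that is not the hazard ratio of the source. Starting from 1.43, PN effects of 1.10 and 1.15 leave 1.43/1.10 = 1.30 and 1.43/1.15 = 1.25 (rounded up from 1.24), roughly the design range.
- A reader might infer that PN receives no credit for navigation in its 10% PrEP rate, because that equals what remains after a 90% drop-off. The article ties the 10% and 20% to 25% reported interest and lower actual uptake, and it knows of no published uptake data in this population. The Background result for navigation concerns viral suppression, not initiation, and does not fix a PN rate.

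**Conclusion.** The point holds as a mislabelled and unsupported effect size. The 64% versus 51% contrast is facilitated care versus standard care in people living with HIV over 10 months; its risk ratio is 1.25 and its hazard ratio about 1.43. It is not an MHU-versus-PN hazard ratio, and it disagrees with the HR of about 2.12 implied for 95% of the sample.

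The 80% power is not shown to be wrong given HR 1.25 to 1.30 and enough events. However, the plan's own rates give about 118 events against the 457 to 631 needed, and power of about 23% to 30% for that HR range. These figures assume proportional hazards, two-sided 0.05, and events only among the 689 retained. How far an active PN arm would reduce the true HR cannot be determined from the article; the PrEP table shows only how strongly power depends on it.

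**What to change.** In Sample size and power calculations:

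1. Describe 64% versus 51% as facilitated linkage versus standard care (risk ratio 1.25, HR about 1.43), and remove the statement that it compares MHU with PN.
2. State the PN and MHU initiation rates assumed for this trial, separately by HIV status and over 6 months, with the reasoning for the PN rate given that PN is an active arm.
3. Convert those rates to an HR. Restate expected events, sidedness, and the power or smallest detectable HR for 864 recruited and 689 retained.
4. Add a sensitivity range for PN uptake, for example 10% to 15% against 20% for MHU.
5. Say that a non-significant result will be read from the confidence interval for MHU versus PN, which the Analytic plan already reports, and not as evidence against a literature-based HR of 1.25.

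The cost is one rewritten paragraph and a short power table. Enrolment need not change. The downside is a less favourable stated power.
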